## Background

Bronchopulmonary dysplasia (BPD) is a common chronic lung disease whose incidence is increasing annually, especially in this time of the two-child policy in China [1, 2]. Patients with BPD usually have ventilator or oxygen dependence during the early stage of the disease [3]. Most patients can gradually withdraw from the ventilator or stop oxygen treatment at different times depending on disease severity, but abnormalities in pulmonary structure and lung function may last until late childhood and even adulthood, especially in those who are diagnosed as severe BPD according to the diagnostic criteria of the National Institute of Child Health and Human Development (NICHD) [4, 5]. The mortality of overall BPD patients is about 15% [6]; nevertheless, the mortality rate of severe BPD reaches 41%, creating an enormous threat to the health of these children [4, 7]. More than 50% of survivors with BPD experience hospital readmission for repeated lower respiratory infections in the first year or two, which causes serious economic and labor burdens on families [4, 8]. Although surfactant treatment [9], prenatal steroid usage [1, 10], ventilator strategies [11], and improved nutrition [12] are used in BPD patients, effective therapies are lacking [13]. Therefore, identifying novel effective therapies for severe BPD in children is urgent and significant.

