### Outcome evaluation

The outcome measures and their time frames of this trial are listed in Table 3. The primary endpoint is the cumulative duration of oxygen therapy, i.e., the duration from starting to stopping oxygen treatment.

**Table 3 Tab3:** Outcome measures

Measures			Time frames
Primary outcomes	Cumulative duration of oxygen therapy		Until the time of stopping oxygen therapy
Secondary outcomes	Adverse events	Number of serious adverse events	Within 24 h post hUC-MSCs infusion
		Acute infusion associated adverse events	From the start of the trials to 1 month post hUC-MSCs infusion
		Late infusion associated adverse events	Within 2 years post hUC-MSCs infusion
	The rate of supplemental oxygen therapy		At 1 month post hUC-MSCs infusion
	Duration of invasive mechanical ventilation		
	Duration of noninvasive mechanical ventilation		
	The first time of stopping oxygen supplement		
	The rate of re-oxygen supplement		
	Pulmonary function changes		At 6, 12, and 24 months post hUC-MSCs infusion
	Chest radiography changes		
	Blood oxygen saturation		At 1, 3, 6, 12, and 24 months post hUC-MSCs infusion
	Mortality		
	Times of hospital readmissions		
	Complications of preterm birth		

The secondary endpoints include the safety and efficacy outcomes. The safety of the study will be assessed by the number of AEs including SAEs, acute infusion-associated AEs (AIA-AEs) and late infusion-associated AEs (LIA-AEs). SAEs include death, any malignant cardiac event (new ventricular tachycardia, ventricular fibrillation, or asystole, cardiac arrest), acute pulmonary embolism, stroke, anaphylactic shock, acute transplant rejection, and any other diseases extending the hospital stay. AIA-AEs include fever, general allergic reaction (rash, edema, erythema, pallor), infection at the injection site, vital sign changes, laboratory test changes (indicators of liver and kidney function, cardiac markers, indicators of hematology and immunity, markers of hepatitis/syphilis/HIV/tuberculosis, and urinalysis). LIA-AEs include tumorigenic events (tumor formation) and teratogenic events.

The efficacy endpoints are as follows: duration of oxygen therapy, duration of invasive mechanical ventilation, duration of noninvasive mechanical ventilation, the first time stopping the supplemental oxygen, rate of re-oxygen supplement, blood oxygen saturation, chest radiography changes, pulmonary function changes, mortality, number of hospital readmissions, and preterm birth complications.

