### Statistical analysis

SPSS version 17 (SPSS Inc., Chicago, IL, USA) statistical analysis software will be used to analyze the data in the study. Significant differences will be considered at an α level of 0.05.

The data will be examined at group assignment to the intervention and control groups using the *χ*^2^ test, *t* test or analysis of variance (ANOVA). For the intervention and control groups, the indicators at baseline and at 1 day, 3 days, 7 days, 1 month, 3 months, 6 months, 12 months, and 24 months will be compared with repeated measures ANOVA. Comparison of these outcome indicators including duration of oxygen therapy, duration of mechanical ventilation, pulmonary function tests, and quantitative scores of chest radiography changes between the intervention and control groups will be conducted using the *t* test. Mortality and hospital readmission rates will be tested by the *χ*^2^ test, while 24-month mortality will be analyzed by Kaplan-Meier curves.

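### Readmission is defined as a count, but the stated chi-square test uses only whether a child was ever readmitted, so the named secondary endpoint is not analysed

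*Protocol article*

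**What the plan says.** Under Outcome evaluation, Table 3 lists "Times of hospital readmissions" among the secondary outcomes. It sits in the block of rows whose time frame reads "At 1, 3, 6, 12, and 24 months post hUC-MSCs infusion". The list of efficacy endpoints in the same section ends with "mortality, number of hospital readmissions, and preterm birth complications". Both places describe a count per child.

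The Statistical analysis section names another quantity and fixes a test for it: "Mortality and hospital readmission rates will be tested by the" chi-square test. Time to event is handled for death only, "while 24-month mortality will be analyzed by Kaplan-Meier curves". Nothing in that section analyses the number of readmissions or allows for time alive and under observation, and no denominator is given for the readmission rate.

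The Background says that more than 50% of survivors with BPD "experience hospital readmission for repeated lower respiratory infections in the first year or two", and puts mortality at about 15% in BPD overall and up to 41% in severe BPD.

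**The concern.** A chi-square test needs each child in one category, so a rate tested this way is naturally the proportion with at least one readmission. A child admitted once and a child admitted five times then count the same. The Background leads one to expect repeat admissions, which are what the count endpoint would capture.

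The second issue is time at risk. A child who dies at three months has had little chance to be readmitted. If that child stays in the denominator as not readmitted, an arm with more deaths shows fewer readmissions for that reason alone.

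At stake are some power and, in some circumstances, the direction of a secondary comparison. The primary outcome is unaffected. The mismatch is not a detail left to an analysis plan, because the article itself names the endpoint and names a test that does not fit it.

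**Working it through.** **The plan's own figure.** The article gives no calculation for readmission. Its sample size is for oxygen duration and it reproduces (two-sided 0.05, power 0.80, SD 15 days):

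- n = 2 × (1.960 + 0.842)² × 15² / difference².
- 13 days (90 to 77): 2 × 7.849 × 225 / 169 = 20.9, so 21.
- 18 days (90 to 72): 2 × 7.849 × 225 / 324 = 10.9, so 11.
- The larger is 21; 21 / 0.9 = 23.3, so 24 per arm and 72 in total.

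This figure is not in dispute. It fixes 24 per arm for what follows.

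**What chi-square retains.** Assume gamma-Poisson counts with mean μ over 24 months and dispersion k. Neither is in the documents. With no deaths, P(ever readmitted) = 1 − (1 + kμ)^(−1/k). With k = 0.8:

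- μ = 2: 1 − 2.6^(−1.25) = 0.70. Halved to μ = 1: 1 − 1.8^(−1.25) = 0.52.
- μ = 0.926: 1 − 1.741^(−1.25) = 0.50. Halved to μ = 0.463: 1 − 1.370^(−1.25) = 0.33.

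A halved admission rate therefore appears to the chi-square test as 70% v 52%, or 50% v 33%.

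**Power, by simulation.** 24 per arm, no deaths; uncorrected chi-square on any readmission against a quasi-Poisson rate model with log time offset and t reference.

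| Controls ever readmitted | True effect | Dispersion | Chi-square | Rate model |
|---|---|---|---|---|
| 50% | rate halved | 0 | 0.33 | 0.35 |
| 50% | rate halved | 0.8 | 0.24 | 0.30 |
| 63% (μ = 1.5) | rate halved | 0.8 | 0.27 | 0.40 |
| 70% (μ = 2) | rate halved | 0.8 | 0.25 | 0.46 |
| 70% (μ = 2) | 60% fewer | 0.8 | 0.41 | 0.65 |

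Separate runs with robust-variance tests agree: at 50% ever readmitted and dispersion 1, 0.22 v 0.28 to 0.30; at 70% and dispersion 1, 0.23 v 0.44 to 0.48.

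**Deaths.** Equal true admission rates in both arms, dispersion 0.8, 50% to 70% of controls ever readmitted if none died, nominal error 5%, and children who die kept in the denominator unless stated.

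| Mortality (assumed) | Timing of deaths | Chi-square error |
|---|---|---|
| 41% v 15% | all in year 1 | 10% to 12% |
| 41% v 15% | spread over 24 months | 8% to 9% |
| 20% v 10% | either | about 6% to 7% |
| 41% v 41% | either | about 6% |
| 41% v 15%, survivors only | either | about 5% |

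In the first row with μ = 1.5, the share ever readmitted is 48% in the arm with 41% mortality and 57% in the arm with 15%, although the admission rates are identical. The rate model's error at 41% v 15% is about 5% to 6%.

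**Another reading of the test.** If chi-square were applied to total admissions per arm, repeats would be kept, but a child's admissions would be treated as independent. At 50% ever readmitted with no deaths, the error would be about 16% at dispersion 1 and 31% at dispersion 2. This reading does not rescue the plan.

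**The case against.** The strongest reply is that this is one of many unpowered secondary outcomes in a trial the Discussion calls exploratory, and that the proportion ever readmitted is a legitimate and easily read summary. That stands. It limits the weight of the point but does not make the stated test fit the stated endpoint.

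Two stronger readings are tempting, and the documents do not support them.

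- A reader might infer that the chi-square test throws away most of the information. The only anchor in the article is more than 50% readmitted, for BPD survivors generally. Near 50% the loss is a few points, and it becomes large only towards 70% and above. Even the rate model has power of only about 0.3 to 0.5 for a halved rate at dispersion 0.8.
- A reader might infer that the plan biases the comparison by counting children who die as never readmitted. The Statistical analysis section states no denominator. The Background speaks of readmission among survivors, and the Withdrawal section lists death as a reason for discontinuation and provides for replacing withdrawn participants. Nor does the article project a mortality difference. The 41% and 15% are its figures for severe and overall BPD, not for two arms, and the exclusion criteria remove some of the sickest children.

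It is also fair to say that the rate model is not free of assumptions. The offset treats death as independent of admission risk within arm. If sicker infants have more of both, the rate ratio is biased: a simulation with shared frailty, no true effect and mortality 41% v 15% gave a rate ratio of about 1.13 against the arm with fewer deaths, with error still near 5%.

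**Conclusion.** The mismatch holds: the endpoint is a count in two places, and the only stated test does not analyse it. The consequence is modest and conditional.

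- **Power.** For a halved rate with 24 per arm and dispersion 0.8, about 0.25 against 0.45 when about 70% of controls are readmitted. At about 50% the difference is some 2 to 6 points for dispersion between 0 and 0.8. Admission means and dispersion are assumptions.
- **Bias.** Only if children who die stay in the denominator and mortality differs widely. Then the arm with more deaths looks better on readmission, and error rises to about 8% to 12% at an assumed 41% v 15%. With equal or modestly different mortality, or among survivors with death independent of admission risk, there is no material bias.

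This is a minor improvement to a secondary analysis and does not threaten the trial's main conclusion.

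**What to change.** Change the readmission line in the Statistical analysis section as follows.

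- Analyse the number of readmissions to 24 months by negative binomial or quasi-Poisson regression, with arm as factor and log time alive and followed as offset.
- Report the rate ratio with its 95% CI, and the number of deaths per arm beside it.
- Keep the proportion ever readmitted as a descriptive summary, with its denominator stated.
- State as a limitation that the model assumes death is independent of admission risk within arm.

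The cost is one changed line and slightly more analysis work. Table 3 already lists the count as an outcome, and the Kaplan-Meier analysis already needs dates of death. Table 2 has no row for readmission and the contents of Tables 4 and 5 are not shown, so it is worth confirming that the follow-up forms record the number of admissions and the date last followed. The change does not make the endpoint confirmatory.

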## Discussion

At present, apart from symptomatic supportive therapy, there is no effective treatment for severe BPD patients [33]. Therefore, identifying new treatment methods to improve the prognosis of premature infants is imperative. Studies have shown that stem-cell therapy can significantly improve neonatal hyperoxic lung injury [34, 35], suggesting that stem-cell transplantation may be a promising treatment for severe BPD.

The intratracheal administration of MSCs in premature infants at high risk of BPD has been investigated in several small uncontrolled studies registered at ClinicalTrials.gov. These studies aim to investigate whether local regional hUC-MSC delivery to the airway is safe and potentially effective and could prevent BPD in premature infants. However, most patients with severe BPD only receive oxygen treatment when a medical ventilator was no longer used. Intratracheal hUC-MSC treatment is difficult to administer to patients under these circumstances. Hence, intravenous administration may be a better choice. Recent studies have shown that the intravenous administration of MSCs was safe and had some potential efficacy in several lung diseases, including acute respiratory distress syndrome (ARDS) and chronic pulmonary disease (COPD) [27, 28], but there are few reports on BPD. Based on these studies, the intravenous administration of MSCs is expected to be a worthwhile option for patients with severe BPD. Considering that hUC-MSCs are a main source in clinical trials, this trial aims to evaluate whether allogeneic hUC-MSC therapy is safe and effective in severe BPD patients with a matched control. We hypothesized that this research will provide data showing that hUC-MSC administration is safe and feasible for severe BPD patients.

A variety of studies on hUC-MSC clinical trials performed a dose-escalation of hUC-MSCs of 0.5–5 million cells/kg in adults through intravenous infusions; the largest dose of a few trials reached 10 million cells/kg [27, 28, 36, 37]. However, few trial reports explored the effect of different doses of hUC-MSCs in children’s diseases, especially in those with severe BPD. Thus, we will conduct a dose-escalation trial of intravenously administered hUC-MSCs for the treatment of severe BPD patients. Considering that the features of premature infants include low weight and immature organ function, we determined a maximum hUC-MSC dose of 5 million cells/kg.

Although this planned trial cannot use a high-quality randomized controlled trial design since it is an open-label trial, it has several advantages. First, this is a first trial to investigate the therapeutic rather than preventive effects of hUC-MSCs in children with severe BPD. Second, this study will explore a dose-escalation of hUC-MSC treatment through intravenous administration. Third, if we can observe some efficacy, our results may broaden our understanding of hUC-MSC effects in BPD and provide a basis for treating patients with severe BPD. However, if there are no obvious effects, our study will also have important clinical implications for pediatric refractory diseases. As several kinds of patients currently receive MSC therapy for which potential efficacy has been reported [29], randomized trials are lacking to prove its safety or efficacy.

Overall, the MSC-BPD trial is a vital and exploratory step in the investigation of a new evidence-based therapy for a large number of pediatric BPD patients.

## Trial status

Start date: July 2019.

Expected end date: December 2021.

Status at time of submission of this article: not yet recruiting.

## Data Availability

All the data in the trial will be available for anyone who wants to access the data following publication.

## Abbreviations

AEs: Adverse events
AIA-AEs: Acute infusion-associated adverse events
ANOVA: Analysis of variance
ARDS: Acute respiratory distress syndrome
BPD: Bronchopulmonary dysplasia
CHCMU: Children’s Hospital of Chongqing Medical University
COPD: Chronic obstructive pulmonary disease
DSMB: Data and Safety Monitoring Board
EUBIO: Ever Union Biotechnology Co. Ltd.
hUC-MSCs: Human umbilical-cord mesenchymal stem cells
LIA-AEs: Late infusion-associated adverse events
MSCs: Mesenchymal stem cells
NICHD: National Institute of Child Health and Human Development
SAEs: Severe adverse events
UC: Umbilical cord
